### Follow-up measurements

Field staff will conduct follow-up surveys in all intervention and control households at 3, 6, 12, 18 and 24 months (Table 2). They will conduct household surveys, blood spot and stool collection in the full study sample (N=800). The following potential mediators and outcomes will be measured in subsamples: maternal bandwidth, time use and child cognitive development (N=400), environmental samples (N=400 for STH by qPCR, N=110 for STH larvation detected using microscopy, N=110 for *E. coli*, N=110 for extended-spectrum beta-lactamase producing *E. coli*), video observations (N=60) (Figure 2). When selecting subsamples of households for additional measurements, households will be randomly selected stratified by geographic block and study arm. Additional subsamples will be nested within the largest group. The same subsamples will be used across follow-up rounds for those with repeated measures. If any of the households included in the subsamples are lost to follow-up at a particular measurement, they will be replaced with another block-stratified randomly sampled household from the same study arm.

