At the 6 month follow-up only, field staff will collect additional samples in a subset (N=110). This will provide an early assessment of intervention effectiveness on a wider range of matrices as well as detect additional sources of contamination in the domestic environment. The additional sample types include: drinking water (for index child or other children <5 years), prepared food (for index child or other children <5 years), floor soil (in control arm only), courtyard soil, and cow and chicken feces from animals that stay in the compound. To collect drinking water, field staff will ask the caregiver to bring them a glass of water the same way they would give it to the index child, or to another child <5 years if the index child is not yet drinking water. Staff will pour approximately 250 mL of water from the glass into a sterile Whirlpak bag. To collect prepared food, staff will ask the caregiver to bring them a small portion of food the same way they would give it to the index child, or to another child <5 years if the index child is not yet eating food. Staff will use a 50 mL sterile tube with a sterile spoon to collect approximately 50 g of food. To collect floor soil, field staff will use a sterilized metal stencil to mark an additional 0.5 m x 0.5 m floor area near the child’s sleeping area as described above. They will scrape a 5 mL sterile tube along a horizontal line within the stencil to collect approximately 5 g of sample for sequencing. They will then use a 50 mL sterile tube with a sterile spoon to scrape the remaining area within the stencil once vertically and once horizontally; they will repeat these steps until the tube is full to obtain approximately 50 g of sample to determine moisture content and soil type. To collect courtyard soil, field staff will use a sterilized metal stencil to mark a 0.3 m x 0.3 m area at the entrance to the household where the index child lives and follow the same procedure as floor soil collection. To collect cow and chicken feces, field staff will ask the caregiver to identify feces from recent defecation by their animals, then use a 50 mL sterile tube with a sterile spoon to collect the fecal sample. Zymo DNA/RNA Shield (Zymo Research, Irvine, California) will be added immediately after collection to sample aliquots that will be used for metagenomic sequencing. All samples will be transported on ice to the icddr,b laboratory in Dhaka. Samples that will be used for molecular analyses will immediately be stored at −80°C until DNA extraction. Samples that will be used for culture-based analyses will be stored at 4°C overnight prior to analysis by the next day.

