In the same subsample (N=110), we will perform metagenomic sequencing of child stool, floor soil, cow feces and chicken feces samples from each follow-up round. Floor soil will only be collected from control arm households (N=55) because we expect that the quantity of soil needed for DNA extraction (10 g) will not be available on concrete floors. We will combine 10 fecal samples of each type and 5 floor soil samples to generate 11 composite samples of each type. We will extract DNA from each composite sample using DNeasy PowerMax Soil Kits for soil samples and Qiagen QIAamp PowerFecal Pro DNA Kits for stool samples. Metagenomic shotgun sequencing will be performed using the Illumina platform. We will use Kraken2 (Wood, Lu, and Langmead 2019) to perform taxonomic classification of reads to identify pathogens and bacterial antimicrobial resistance genes in each sample.

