### Statistical analysis

To assess randomisation, we will compare the means and percentages of baseline characteristics between arms including maternal age, maternal education level, paternal education, paternal employment, housing wall and roof materials, household assets, acres of homestead land owned, household WASH infrastructure and access, open defecation practices, and deworming in the prior 6 months, animal ownership, and animal cohabitation.

The primary analysis will compare prevalence of any STH between study arms using an indicator for whether a child tested positive at the 6, 12, 18, or 24 month follow-up rounds. We will estimate the unadjusted prevalence ratio comparing intervention to control using generalized estimating equations (Zeger, Liang, and Albert 1988) with a binomial family and log link and an exchangeable correlation matrix to account for repeated measures within the same child. If log-binomial models do not converge, we will use modified Poisson regression with robust standard errors (Zou 2004). Secondary analyses will include indicators for follow-up rounds in order to estimate the prevalence ratio at each follow-up to assess whether effects vary over different child ages. All models will condition on geographic block and estimate robust sandwich standard errors (Freedman 2006) to account for the matched design (McNutt et al. 2003; Kernan et al. 1999). To assess whether the intervention effect is sustained over 2 years, we will also fit a model with an interaction term between treatment and follow-up time.

We will also compare secondary outcomes (Table 1) between study arms. For repeated measures outcomes, we will use generalized estimating equations (Zeger, Liang, and Albert 1988) with an exchangeable correlation matrix; we will estimate mean differences for continuous outcomes using an identity link and Gaussian family and prevalence ratios for binary outcomes using a log link and binomial family (McNutt et al. 2003). For measurements analyzed at a single time point, we will fit generalized linear models (McNutt et al. 2003) with a Gaussian family and identity link for continuous outcomes and a binomial family and log link for binary outcomes. If log-binomial models do not converge, we will fit models with a Poisson and log link (McNutt et al. 2003; Zou 2004).

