**Figure 3. F3:**
[figure not shown]
CRADLE Study site map A) Map of study site location within Sirajganj and Tangail districts, Bangladesh. B) Exterior boundary of unions included in the study site in Chauhali, Belkuchi, and Nagarpur unions of Sirajganj and Tangail districts. Base map source: Esri.

**Table 1. T1:** Outcome measures

Primary outcome	
Prevalence of any soil-transmitted helminth using qPCR	Proportion of children in which *Ascaris lumbricoides, Necator americanus, or Trichuris trichiura* was detected in stool by qPCR at any follow-up measurement (6, 12, 18, or 24 months of age).
Secondary outcomes	
*Child health outcomes*	
Prevalence of *Ascaris lumbricoides, Necator americanus* or *Trichuris trichiura* using qPCR	Proportion of children in which *Ascaris lumbricoides, Necator americanus* or *Trichuris trichiura* was detected in stool by qPCR at any follow-up measurement (6, 12, 18, or 24 months of age).
Mean *Ascaris lumbricoides, Necator americanus* and *Trichuris trichiura* eggs per gram	Geometric and arithmetic mean of *Ascaris lumbricoides, Necator americanus* and *Trichuris trichiura* eggs per gram detected in stool by Kato-Katz at any follow-up measurement (6, 12, 18, or 24 months of age)
Diarrhea prevalence	Prevalence of caregiver-reported and stool consistency based child diarrhea in the past 7 days (at least three loose or watery stools within 24 hours or at least one bloody stool) at any follow-up measurement (6, 12, 18, or 24 months of age)
Relative abundance and diversity of human pathogens	Human pathogens detected in child stool using shotgun metagenomic sequencing each follow-up round
Relative abundance and diversity of antimicrobial resistance genes	Antimicrobial resistance genes detected in child stool using shotgun metagenomic sequencing each follow-up round
*Child behavior*	
Rate of child soil contact and ingestion	Mean number of soil contact and ingestion events per child-hour observed during 6-hour video observations at each follow-up (6, 12, 18, 24 months)
*Child development outcomes*	
Mean ASQi score at 12 and 24 months	Mean communication, fine motor, gross motor, problem solving, personal-social and combined scores measured using the Ages and Stages Inventory calculated separately at 12 months and 24 months
Mean overall Family Care Indicator score at 12 and 24 months	Mean Family Care Indicator score overall measured separately at 12 months and 24 months (range: 0-3)
*Maternal outcomes*	

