Most probable number of cefotaxime-resistant *E. coli* in household floor samples	Cefotaxime-resistant *E. coli* enumerated by IDEXX with cefotaxime supplement in household floor swabs at any follow-up measurement (6, 12, 18, 24 months)
Prevalence of extended-spectrum beta-lactamase producing *E. coli* (ESBL-E) and ESBL coding genes in household floor samples, courtyard soil, child hand rinses, drinking water, prepared food, cow feces and chicken feces	ESBL-E and ESBL coding genes in floor swabs, courtyard soil, child hand rinses, drinking water, prepared food, cow feces and chicken feces at 6 months follow-up
Mass of floor dust (g per m^2^)	Mass of dust on floors collected by sweeping a 2 m^2^ floor area next to bed where child sleeps at night (6, 12, 18, 24 months)
Relative abundance and diversity of human pathogens	Human pathogens detected in floor soil, cow feces and chicken feces samples using shotgun metagenomic sequencing each follow-up round
Relative abundance and diversity of antimicrobial resistance genes	Antimicrobial resistance genes detected in floor soil, cow feces and chicken feces samples using shotgun metagenomic sequencing each follow-up round
*Floor outcomes*	
Rate of floor sweeping and refinishing	Mean number of times floors were swept per household-day at each follow-up measurement and mean number of times floors were refinished per household-month at each follow-up measurement (6, 12, 18, 24 months)
Prevalence of holes or cracks in household floors	Proportion of household floors with holes or cracks at each follow-up measurement (6, 12, 18, 24 months)
Prevalence of impermeable household floors	Proportion of household floors in which surface water was still present after 1 minute at each follow-up measurement (6, 12, 18, 24 months)

**Table 2: T2:** Summary of variables measured in surveys

		Baseline	Birth	3 mo.	6 mo.	12 mo.	18 mo.	24 mo.
Household characteristics	Household construction materials	X			X	X	X	X
	Household census	X			X	X	X	X
	Household assets	X			X	X	X	X
	Parental education and employment	X			X			X
	WASH infrastructure & practices	X			X	X	X	X
	Animal ownership & husbandry	X			X	X	X	X
	Animal presence in the home	X			X	X	X	X
	Human and animal feces in the home	X			X	X	X	X
Perinatal outcomes	Prenatal and birth outcomes		X					
Anthropometry	Length, weight, head circumference	X	X	X	X	X	X	X
Illness symptoms	Child illness symptoms (e.g., diarrhea)	X			X	X	X	X
Flooring	Floor durability assessment	X			X	X	X	X

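### Fecal composites of 10 do not fit 55 households per arm, so at least one must mix arms; floor soil has no between-arm contrast, and the sampling rounds for soil and animal feces conflict

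*Protocol article*

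**What the plan says.** All references are to the protocol article.

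- **Sample and timing of sequencing (Laboratory assays):** "In the same subsample (N=110), we will perform metagenomic sequencing of child stool, floor soil, cow feces and chicken feces samples from each follow-up round".
- **Arm restriction on soil (Laboratory assays):** "Floor soil will only be collected from control arm households (N=55"), because too little soil is expected on concrete. Environmental sample collection repeats the control-only restriction.
- **Pooling rule (Laboratory assays):** "We will combine 10 fecal samples of each type and 5 floor soil samples to generate 11 composite samples of each type". How households are assigned to pools is not stated.
- **Timing of collection (Environmental sample collection):** "At the 6 month follow-up only, field staff will collect additional samples in a subset (N=110"). The list that follows includes floor soil and cow and chicken feces. The Figure 2 legend also places these at 6 months.
- **Outcomes (Table 1):** for child stool, "Human pathogens detected in child stool using shotgun metagenomic sequencing each follow-up round"; for the environment, "Human pathogens detected in floor soil, cow feces and chicken feces samples using shotgun metagenomic sequencing each follow-up round". Each has a parallel row for antimicrobial resistance genes, which makes four metagenomic rows.
- **Analysis (Statistical analysis):** "We will also compare secondary outcomes (Table 1) between study arms".
- **Selection of subsamples (Follow-up measurements):** "households will be randomly selected stratified by geographic block and study arm".

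**The concern.** Pooling replaces household results with one result per composite. A between-arm comparison then needs each composite to belong to one arm; a composite holding equal numbers from both arms says nothing about treatment. The stated pool size and number of composites cannot be met without at least one mixed composite, and nothing stated limits mixing to that one.

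Two further points bear on the same four Table 1 rows. Floor soil exists in one arm only, so a general instruction to compare Table 1 outcomes by arm cannot be carried out for it. And the two environmental rows require sequencing at rounds for which the collection section provides no floor soil or animal feces.

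At stake are the metagenomic secondary outcomes: how many composites can inform the treatment effect, at which ages, and for which sample types.

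**Working it through.** **Inputs.** Subsample 110; control 55; fecal pool size 10; soil pool size 5; composites of each type 11 (all Laboratory assays). Intervention households: 110 − 55 = 55. This figure is implied rather than stated, and agrees with selection stratified by arm. One sample of each fecal type per household and round is assumed.

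**1. The plan's own figure.** Fecal: 110/10 = 11. Floor soil: 55/5 = 11. Both reproduce the stated 11.

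**2. Arm purity.** Per arm, 55 = 5 × 10 + 5. At most 5 full single-arm composites can be made per arm, 10 in all. The remaining 11 − 10 = 1 composite takes the 5 left over from each arm. So the number of mixed composites per fecal type and round is at least 1 and at most 11. In the best case 100 of 110 samples inform the contrast.

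**3. If pooling ignored arm.** The chance that a given composite of 10 is single-arm is 2 × C(55,10)/C(110,10) = 0.0012. The expected number of single-arm composites among 11 is 11 × 0.0012 ≈ 0.01, so practically all would be mixed.

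**4. Pool sizes that divide 55.** Size 11: 55/11 = 5 per arm, 10 composites per type. Size 5: 55/5 = 11 per arm, 22 composites per type.

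**5. Precision with the composite as the unit.** Two-sample t-test, two-sided 0.05, power 0.80:

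| Composites per arm | Detectable difference (between-composite SD) |
|---|---|
| 5 | 2.02 |
| 11 | 1.26 |

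The two rows are not on one scale, because larger pools vary less. If a composite behaved as the average of independent households with no laboratory variation, its SD would be the household SD divided by the square root of the pool size. The detectable differences would then be 2.02/√11 = 0.61 household SDs (5 pools of 11 per arm) and 1.26/√5 = 0.56 (11 pools of 5 per arm). The advantage of smaller pools may therefore be modest. With 5 against 5, the smallest two-sided exact p-value for one comparison is 2/C(10,5) = 2/252 = 0.008, before any allowance for many taxa or genes.

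**6. Rounds, side by side.**

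| Sample | To be sequenced (Laboratory assays, Table 1) | Collected |
|---|---|---|
| Child stool | every round | 6, 12, 18, 24 months (Stool collection) |
| Floor soil, cow feces, chicken feces | every round | 6 months only (Environmental sample collection) |

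The Table 1 row for ESBL-producing *E. coli* also limits cow and chicken feces to 6 months. Taking every round to mean the four stool rounds, the sequencing text implies 4 types × 11 × 4 = 176 composites. The collection text supports 11 × 4 + 3 × 11 = 77.

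**The case against.** The strongest reply is that a journal article condenses the full protocol, and the rule for assigning samples to pools may sit in a laboratory procedure. Silence on within-arm pooling is not evidence of mixing. That is fair, and it limits the point. But the single forced mixed composite follows from figures that the article itself fixes, so it does not depend on the silence.

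A reader might go further and infer that all 11 fecal composites are half intervention and half control. Ten fecal samples sit beside five control-only soil samples, and randomisation blocks hold ten households allocated 1:1. The documents do not say that fecal and soil pools share households or follow blocks, and wanting 11 composites of each type explains the numbers equally well. This reading is possible but not established.

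A reader might also conclude that none of the four metagenomic rows can be estimated. That does not follow. Pooling within arm leaves a 5 against 5 contrast for fecal samples, imprecise but estimable. The timing conflict does not touch child stool, and for animal feces it removes the later rounds, not the 6-month contrast. Only floor soil truly lacks a contrast, and the article openly gives the reason for sampling it in one arm.

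Two other replies stand in part. Animal feces depend on animals staying in the compound, so 110 samples may not be reached and the forced mixed composite is less certain for those types; it is firmest for child stool. Nor do the documents say whether individual material survives pooling, so permanent loss of the contrast is not shown.

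**Conclusion.** The point holds in three parts.

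1. With 55 households per arm and full sampling, 11 composites of 10 force at least one mixed-arm composite per fecal type and round. The usable comparison is at best 5 against 5, and it is smaller if pooling ignores arm.
2. Floor-soil metagenomics, included in two Table 1 rows, has no between-arm contrast although Table 1 outcomes are to be compared by arm.
3. Laboratory assays and Table 1 contradict Environmental sample collection on when floor soil and animal feces are available; the Figure 2 legend agrees with the latter.

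This rests on the inferred 55 intervention households and on one sample per household of each fecal type. It concerns secondary outcomes in 110 of 800 households. The primary outcome uses qPCR on stool and is unaffected. It should be corrected before any pooling, but it does not threaten the trial's main conclusion.

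**What to change.** - **Pooling.** State that fecal composites are formed strictly within arm and within round, with a size that divides 55. Five pools of 11 per arm give 10 composites per type, one fewer than planned, at no added cost. Eleven pools of 5 per arm give 22, at double the sequencing libraries. Say what happens when fewer than 55 samples of a type are obtained in an arm.
- **Analysis.** Name the composite as the unit of analysis and acknowledge the low precision. Pools of 11 do not yield more pure composites than the best case now; they use every sample and remove the doubt about mixing.
- **Floor soil.** Label its metagenomic results as control-only and descriptive, and exclude them from the between-arm comparison.
- **Rounds.** Reconcile Laboratory assays, Environmental sample collection, the Figure 2 legend and the two environmental metagenomic rows of Table 1. If collection stays at 6 months only, this is a text correction. If every round is intended, it adds collection and sequencing at 12, 18 and 24 months.

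With pools of 11 and 6-month collection, the cost is a change to the laboratory procedure and the wording.

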### Maternal measures

We will measure maternal stress, depression, and time use at child ages 3 and 12 months and maternal bandwidth at child ages 6 and 18 months. This sequencing will minimize participant fatigue by reducing the number of measures collected per round and will ensure that mediators are measured prior to each child cognitive measurement at 12 and 24 months.

Maternal bandwidth measures will include visual-spatial working memory, executive function, inhibitory control, and cognitive flexibility and attention shifting. To measure visual-spatial working memory, we will use an analog version of the Corsi Block Span Task (Berch, Krikorian, and Huha 1998) since mothers may be unfamiliar with computers or tablets. The analog version is a customized set of blocks located in fixed positions on a board. An enumerator will tap on a sequence of blocks and mothers will be asked to recall the sequence by tapping the blocks. Sequence length will increase in each round, with a maximum sequence length of nine blocks for the forwards Corsi task and eight blocks for the backwards Corsi task, where the mother recalls the sequence in the reverse order. Field staff will record the maximum sequence length correctly recalled by the mother.

We will measure perception, abstraction capacity, analogical reasoning and metacognitive executive function except emotion using Raven’s Progressive Matrices (Diamond 2013; John and Raven 2003). Each booklet will contain 48 patterns with a missing tile inside. Mothers will have 45 minutes to choose the missing tile that best completes each of the 48 patterns. At the end of the task, the total raw score will be converted to an Ability Score and Standard Score.

We will also measure cognitive inhibition, which refers to the ability to suppress the processing of stimuli that are irrelevant to the intent of the task and inhibit a prepotent response. We will use an adapted version of The Hearts and Flowers task (Davidson et al. 2006) using images of cats and dogs, which are recognizable to the study population. This task takes into account both accuracy and speed and captures individual differences in inhibition and cognitive flexibility (Davidson et al. 2006; Obradović et al. 2017). This task has three rounds, each with 20 trials. In the first round, dogs will appear randomly on either the right or left side of a page, and respondents (mothers) will be asked to respond to one rule: to place their hand over an arrow on the same side of page as a dog image (congruent task). In the second round, cats will appear on either side of the page, and mothers will be asked to place their hand on an arrow on the side opposite to where the cat appears (incongruent task). In the third round, dogs and cats will appear intermixed (mixed task), and mothers will be asked to respond accordingly. Usually, no executive demands are required in the Dog task, thus it is used as a control task to compare performance on the Cat and mixed tasks. The percentage of correct responses and response time will be recorded for each respondent.

To measure cognitive flexibility and attention shifting, we will use Dimensional Change Card Sort (DCCS) test presented as stimuli on flip charts instead of a screen (von Suchodoletz, Slot, and Shroff 2017). Two target pictures will be presented that will vary along two dimensions (e.g., shape and color). The participants will match the picture at the top of the displayed page with two pictures with varied dimensions (e.g., shape and color) at the bottom. To match the picture according to the requested dimension spoken by the tester, participants will place their hand on an arrow at the side of the correct corresponding picture. Following practice trials with color-matching and shape-matching, 29 mixed trials will be offered. We will record the percentage of correct responses and response time for each participant.

To measure maternal discretionary time, we will use a hybrid time diary adapted to our setting in Bangladesh (Erica M. Field, Rohini Pande, Natalia Rigol, Simone G. Schaner, Elena M. Stacy, Charity M. Troyer Moore 2022). Enumerators will invite mothers to summarize the prior day’s activities chronologically and allocate hours by placing tokens next to photos of 9 common activities. This approach does not require mothers to perform calculations or be literate. We will calculate total time spent on each activity to determine discretionary time.

